**Fig. 1 Fig1:**
[figure not shown]
Study flow chart. Standardized Consolidated Standards of Reporting Trials (CONSORT) flow for the Talking Prescription (Talking Rx) program

They will be randomized into two parallel groups (intervention group and control group) in a 1:1 ratio via block technique. Both groups will have access to a helpline number to address their queries regarding their illness and medications in addition to receiving the standard of care as per institutional guidelines. In addition, participants in the intervention group will also have access to Interactive Voice Response (IVR)-based informative voice messages tailored to their respective prescriptions. The intervention group will also receive daily tailored text messages regarding dosage and frequency of intake of statins and anti-platelet medications. They would also receive weekly text message reminders to improve medication adherence, lifestyle changes, medication information, risk factors and motivation to improve adherence. These messages are modeled on Social Cognitive Theory and the Health Belief Model and are categorized by Michie’s Taxonomy of Behavioral Change Communication [5, 6].

Patients’ adherence to medications will be assessed using the Morisky Medication Adherence Scale (MMAS) [7]. In a sub-set of patients (20 % of patients in each group), pill count will be performed to assess the correlation between self-reported MMAS and direct pill count. Patient’s health literacy will be measured at baseline and then after 3 months in each group by using Likert’s Scale for Health Intelligence Literacy, Knowledge of Medications, and a modified version of Test of Health Literacy in Adults (TOFHLA) (modified version) [8–10]. The difference in adherence to medication regimen (and health literacy) before and after the intervention will be compared between the two groups to determine the effectiveness of our intervention.

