### Outcomes: (Additional file 2 − Data Collection Form)

The primary outcome of interest is a change in medication adherence after 3 months of receiving the SMS and being exposed to the Talking Prescription (*Bolta Parcha*). Our secondary outcome is change in health literacy. The findings of the treatment group on these outcomes will be compared to the corresponding findings from the control group to account for the Hawthorne effect.

Medication adherence will be measured at recruitment and after 3 months in both groups using the MMAS. The scale has been used in a similar setting previously and it has been translated and validated in Urdu. The change will be determined by comparing the score on the MMAS before and after the intervention [15].

The instrument consists of eight questions and the response to each question is scored as either 0 (yes) or 1 (no). The maximum score, hence, is 8. A higher score indicates better adherence. A score of less than 2 indicates low adherence.

The secondary outcome measure is assessment of functional health literacy in adults (TOFHLA) which will be assessed at enrollment and then at the follow-up visit after 3 months. This tool has been adapted, modified, and content-validated by a panel of experts, translated and back-translated from English to Urdu, to better represent the Pakistani community and its health system. It consists of two sections: the first section covers questions about the basic instructions for each patient coming to the clinic, and the second section contains three passages comprised of questions about the relevant information every patient visiting the hospital should ideally possess.

Section 1 has a total of 17 questions, where a correct answer merits a score of 1 and an incorrect answer gets a score of 0. First Raw score is obtained after adding responses to each question and this score out of 17 is converted to a weighted score, using a reference table, to a denominator of 50.

Section 2 has a total of 50 questions, where each correct answer earns a score of 1 for the patient and an incorrect answer earns a score of 0. The total score at the end of this section is scored out of 50.

In the end, TOFHLA is evaluated on a total of 100, where health literacy is given a total score ranging between 0 and 59 (inadequate), between 60 and 74 (marginal), and from 75 up to 100 (adequate) [8].

In addition, we will perform sensitivity analyses comparing the correlation between the MMAS and the pill count.

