### Statistical methods

Analysis will be performed using the intention-to-treat principle: an interim analysis after 25 % of the sample has been reached and final analysis after data has been collected from all study participants. Since this is an IT-based intervention, we plan to do an interim analysis to assess technical compliance to intervention, any unexpected side effects like participant fatigue and drop out. We do not expect any serious safety issues to arise as this study only concerns reception of educational intervention.

The use of the intention-to-treat principle for analysis means that all patients will be analyzed in the treatment arm to which they were randomized. Analysis will be performed after the completion of follow-up of all study participants. Protocol deviations and exclusions (with reasons, will be reported for each arm of the trial). Estimates of intervention effects will be presented with 95 % confidence intervals. A two-tailed *P* value of ≤0.05 will be considered statistically significant for the outcome measures.

For descriptive analysis, mean with standard deviation or median with interquartile range will be reported for continuous data. For categorical data, frequency with percentages will be calculated.

The primary outcome analysis will be based on improvement in medication adherence level, assessed by the change in MMAS score at 3 months of follow-up. To report the difference between the mean scores of intervention group and control arm, Student’s *t* test or the Mann-Whitney *U* test will be performed.

To evaluate the secondary outcome, change in functional health literacy assessed by TOFHLA, the difference of proportion between the two arms will be calculated either by Pearson’s chi-square test or Fisher’s exact test.

To evaluate the correlation between adherence to medications and pill counts either Pearson’s correlation or the Spearman rank correlation test will be applied and coefficients will be calculated to report the strength of correlation.

All analysis will be performed on Stata version13.

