Another limitation to the study is the application of the literacy tool TOFHLA in a developing country like Pakistan where the literacy rate varies between 28 and 96 %, varying sharply with age groups and regions. Since Karachi is the largest metropolitan city of the country with population of 9.3 million, literacy rate variations in this city are expected. In addition, the health system in Pakistan is very different to the US where this tool was designed. Hence, TOFHLA was modified and adapted to embrace the limitations encountered in our local community while we adhered to the basic architecture of TOFHLA. First, section 1 was modified to encompass our health system replacing insurance coverage with topics more pertinent to our local health structure. Second, passages in section 2 were completely over-hauled and replaced by our local data and advice by regional content experts. In addition, each statement was kept short and focused with just one blank to decrease the confusion that was anticipated with the presence of three to four blanks in the original version. The total numbers of questions in each section were kept the same to ensure accurate scoring as delineated in the original tool. This modified TOFHLA was content-validated by five experts each, from the fields of neurology, cardiology and epidemiology/statistics. After extensive fine-tuning, this tool was translated in Urdu and thereby successfully tested in the pilot. Our Cumulative Validity Index (CVI) scores for the regionally adapted TOFHLA were as follows: for relevance 0.87 and for clarity 0.72, which are excellent.

This study is regionally important. Pakistan, like other emerging low- and middle-income countries, faces non-communicable diseases like stroke and MI as its major health challenge, so a low-cost intervention would have a high impact [1, 4]. The study population is uniquely at high risk and exceptionally vulnerable to these two vascular diseases. Currently, the country has an electronic database with a unique identifier number, thus the potential of reaching masses as an extension is possible in addition to the already vast mobile infrastructure [43]. Since most out-of-pocket, large, unanticipated expenditure on vascular disease would push most Pakistanis into poverty, simple small steps in prevention would help and, even if the expected effect size is modest, we may ultimately have the potential to empower and positively influence many more lives [44–46].

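### Health literacy is defined as a before-after change in a 0–100 score but is tested as an undefined proportion, which costs power and leaves the comparison open

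*Protocol article*

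**What the plan says.** Under Outcomes the article states "Our secondary outcome is change in health literacy". The instrument is a modified TOFHLA, "which will be assessed at enrollment and then at the follow-up visit after 3 months". Section 1 is converted to 50 points and section 2 is scored out of 50: "In the end, TOFHLA is evaluated on a total of 100". Three bands are given: "between 0 and 59 (inadequate), between 60 and 74 (marginal), and from 75 up to 100 (adequate".

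Design overview (text after Fig. 1) describes the comparison in the same terms: "The difference in adherence to medication regimen (and health literacy) before and after the intervention will be compared between the two groups".

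Statistical methods again calls the outcome a change in functional health literacy, but then says "the difference of proportion between the two arms will be calculated either by" Pearson's chi-square or Fisher's exact test. It names neither the proportion nor the visit. The primary outcome, one paragraph earlier, is analysed as a change in MMAS score by t test or Mann-Whitney.

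On the instrument, the Discussion says section 1 was adapted to the local health system and that "passages in section 2 were completely over-hauled and replaced by our local data". It adds that the number of questions per section was kept so that the original scoring would still apply.

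**The concern.** The outcome as defined and the analysis as fixed do not match. The definition calls for a comparison of change in a score measured twice. The analysis compares proportions with tests that have no place for a covariate. Three consequences follow.

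- **Power.** Improved health literacy is one of the trial's two hypotheses. Collapsing a 0–100 score into bands discards information, and a 3-month band also leaves the enrollment score unused.
- **An open comparison.** The text fits at least four tests: adequate versus not, at least marginal versus not, all three bands, or improved a band versus not. The choice could be made after the data are seen.
- **Dependence on cut-offs.** Any of these rests on thresholds set for the original tool. The section 2 passages have since been replaced, and each statement now has one blank instead of three to four. The validation reported is expert content validity (0.87 for relevance, 0.72 for clarity), translation and a pilot. No calibration of 60 or 75 is described.

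**Working it through.** **1. The plan's own figure.** There is none for TOFHLA: no SD, correlation, proportion or target effect. The only sample-size figure, 86 evaluable per arm, was set for 1 point on MMAS at 90% power and two-sided 5%. It gives no SD either. Solving back, SD = 1 / [(1.960 + 1.282) × √(2/86)] = 2.02. I take 86 per arm and two-sided 5% from the article; everything below about TOFHLA is assumed.

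**2. Formula check, assumed effect d = 0.4 SD.** √(2/86) = 0.1525. For a score analysis, power = Φ(d / (k × 0.1525) − 1.96), where ρ is the correlation between the two visits.

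- 3-month score, t test: k = 1; Φ(2.62 − 1.96) = 75%.
- Change score: k = √(2(1−ρ)); 75% at ρ = 0.5, 92% at ρ = 0.7.
- Regression on arm and baseline: k = √(1−ρ²); 86% at ρ = 0.5 (k = 0.866), 96% at ρ = 0.7 (k = 0.714).
- Dichotomised 3-month score: with 50% of controls above the cut, the intervention share is Φ(0.4) = 65.5% and power is 54%. With 30%, 20% or 10% of controls above the cut, power is 53%, 49% and 38%.

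The efficiency of dichotomising is φ(c)² / [p(1−p)], where p is the control share above cut c: 0.64 at p = 50%, falling to 0.34 at p = 10%. At best, 86 per arm then carries the information of 0.64 × 86 ≈ 55 per arm, before any loss from omitting baseline.

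**3. Simulation with the article's bands.** Bivariate normal scores, rounded and held to 0–100, cut at 60 and 75, 86 per arm, 2,000 or 3,000 trials per setting. Assumed SD 20 and an 8-point effect; power in %:

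| Mean | ρ | Adequate at 3 months | Three bands | Improved a band | Change t test | Regression |
|---|---|---|---|---|---|---|
| 45 | 0.5 | 34 | 44 | 48 | 74 | 84 |
| 45 | 0.7 | 34 | 44 | 55 | 92 | 96 |
| 60 | 0.5 | 52 | 53 | 46 | 73 | 84 |
| 60 | 0.7 | 50 | 54 | 60 | 91 | 96 |
| 70 | 0.5 | 59 | 54 | 31 | 73 | 83 |
| 70 | 0.7 | 58 | 52 | 47 | 90 | 94 |

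Other assumptions, mean 60:

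| SD | ρ | Effect | Three bands | Change t test | Regression | Gain of regression over three bands |
|---|---|---|---|---|---|---|
| 20 | 0.3 | 6 | 33 | 37 | 54 | 21 |
| 20 | 0.3 | 8 | 54 | 59 | 77 | 23 |
| 20 | 0.7 | 6 | 32 | 72 | 78 | 45 (77.6 − 32.2) |
| 20 | 0.5 | 12 | 88 | 97 | 99 | 11 |
| 15 | 0.5 | 10 | 95 | 99 | 100 | 5 |

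The lowest proportion result, about 25%, is the improved-a-band test at SD 20, ρ = 0.3 and 6 points. The largest gain over any proportion test is at mean 45, ρ = 0.7, against adequate at 3 months: 96.1 − 34.3 = 62 points. Regression had the higher power in every setting tried. With no true effect, all the tests rejected in about 4–6% of trials.

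**The case against.** **The proportion may already measure change.** A reader might infer that the planned test ignores baseline and does not measure change at all. The text does not support that: the proportion is undefined and could be the share who moved up a band, which uses baseline through the outcome definition. This stands. What remains is that the article does not say so, and that this version had only about 31–60% power in the first table.

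**The definition may sit in a fuller document.** A condensed article can leave a definition to the full protocol or analysis plan. But the article does not defer the analysis; it names the tests, and tests on proportions are a poor fit to change in a score wherever the proportion is defined.

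**The cut-offs have a stated rationale.** A reader might infer that the bands are invalid for this version. The documents do not show that. Keeping the question counts preserves the 0–100 range, but does not by itself show that 60 or 75 means the same after the rewrite. The total score is no better validated as a scale than the bands are. Its advantage is only that a mean difference does not depend on where thresholds fall.

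**The size is assumed.** This stands. At ρ = 0.3 the change-score t test gains only about 4–5 points over the three-band test, so much of the benefit there comes from baseline adjustment. With large effects, every method does well.

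**The consequence is limited.** This also stands. The outcome is secondary, the study is described as a pilot, the sample size was set on MMAS, and Design overview lists two further literacy measures.

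**Conclusion.** The point holds as a mismatch between a score-change outcome and an undefined proportion test. It is a matter of efficiency and clarity, not of validity: comparing proportions between randomised arms keeps the type I error rate.

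The cost is power. Over assumed means of 45–70, SDs of 15–20, correlations of 0.3–0.7 and effects of 6–12 points, proportion tests reached about 25–95% and baseline-adjusted regression about 54–100%. At a mean of 60 the gain over the three-band test was about 5 to 45 points; it was larger in some settings at other means. None of these inputs is in the article, so only the direction and rough size should be relied on. The change should be made because it is nearly free, but it does not threaten the primary analysis.

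**What to change.** In Statistical methods, replace the sentence on the secondary outcome with: the 3-month TOFHLA total (0–100) will be analysed by linear regression on arm, adjusted for the baseline TOFHLA total, and reported as a mean difference with 95% CI. Keep one category proportion as a supportive summary and define it in advance by band and visit, for example adequate (75 or more) at 3 months. State that the band thresholds come from the original tool and have not been calibrated for the modified version.

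The cost is about one sentence. Both measurements are already planned for every participant, and no visit, form or sample-size change is needed. The article lists the trial as ongoing; the change should be dated and made before outcome data are examined by arm. The article requires ethics committee approval and a report to the registry for protocol changes.

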### Recruitment and retention plan

Patients in the hospital database with diagnoses of stroke or MI are selected, following which their clinical histories are studied in detail to ascertain their eligibility criteria. If a participant is interested in the study, eligibility is assessed during a telephone conversation only. If the patient is found eligible, he or she is given the option of visiting the research facility just for the enrollment interview or to coincide with the interview day with clinical follow-up with the respective consultant at the hospital (in case of an upcoming clinic appointment). In case of difficulty in visiting the facility, free pick up and drop off is offered to patients for the enrollment interview.

In order to retain participants the hotline number is shared for all queries arising during enrollment and participants are thanked for their time during the study. Reminders are sent prior to interview dates and a 2-week margin is given to allow a time suitable for CTU visit. Due to telephone contact we will be able to collect data on reasons for participant discontinuation, loss to follow-up, etc.

### Ethics and human subjects’ protection

All patients taking part in the trial will be required to provide written informed consent at the time of recruitment after thorough counseling by the trial-trained research associate, who is a research associate.

Consent forms have been approved by the Ethical Review Committee (ERC) at AKUH and are available in English and Urdu. The participants will have the right to withdraw at any time during the study. In addition, their inclusion or exclusion from the study will not affect the usual standard care provided to them. Participants will be financially reimbursed for all costs pertaining to their follow-up visits. Participants identified as having depression and dementia will be referred to appropriate physicians for further management (see Additional file 3 – Informed Consent Form).

In addition, special care is taken to maintain patient confidentiality. Health promotional texts will be sent once weekly at times that do not inconvenience the patient such as late at night.

In days of high security alerts in the city and announced SMS blackouts, it is planned to send an advanced SMS the night before to the participant so that there would not be any SMS the next day, hopefully avoiding participant anxiety or uncertainty about continuity of care or reception of services.

All team members have received Good Clinical Practice (GCP) training and a face-to-face training, in a 2-day neuroethics course regarding research in the developing world, where all design aspects for this trial were discussed.

The protocol has been approved by the ERC of the Aga Khan University. The study Ethical Review Number is 3165-MED-ERC_14. Any changes to the protocol will need to be approved by the ERC before implementation and reported to the trial registry at https://clinicaltrials.gov.

Six-monthly reviews on the progress of the trial will be conducted by the ERC including inspection of signed informed consent forms and the study will comply with all ongoing audits for local regulatory compliance.

### Access and dissemination policy

Only the collaborating principal investigators and research team will have access to the study results and will be responsible for publishing them in a timely manner. The funding source will not have any special access or privileges regarding results before publication. The ERC will be given access to data if required. Results will be disseminated through scientific journals, conferences and meetings.

## Discussion

This study protocol presents the design of a randomized controlled trial using Talking Prescriptions for improving medication adherence and health literacy in patients with stroke or CAD.

Technology has been used to increase medication adherence to HIV medications, polio vaccination, and most asthma, hypertension and maternal and child care interventions in developed world populations [19–27]. In general, SMS is the most common technology used for these interventions. This is a patient-centered intervention which is friendly, repeatable and accessible and requires no advanced literacy.

There are several unique aspects to this protocol. First, technology has never been used in a unique high-risk vascular disease population living in resource-strapped settings with marginal support and poor health literacy [28–31]. Second, the content used in this intervention are not just simple knowledge transfer texts, the wording and the content has been designed based on the Health Belief Theory and Social Cognitive Model [32, 33]. Third, each behavioral communication message is informed by taxonomy and coded for easy replicability of intervention [6]. Fourth, our study protocol, design and methods are robust by the use of centralized randomization, allocation concealment, blinded assessment, intention-to-treat analysis, and a design to ensure maximum follow-up and minimize attrition [34–36].

The major limitation of this study is the choice of measure of primary outcome, i.e., self-report of medication adherence on the Morisky Medication Adherence Questionnaire [37, 38]. Although this tool has been validated in Urdu in the implementation country, using assessment tools such as biochemical markers or electronic pill boxes may potentially provide more accurate results. This however is not possible because of the complexity of a vascular patient’s prescription; this may include drugs for multiple risk factors and multiple drugs at the same time. Simply opening an electronic pill box registers a dose as administered even if the patient takes only two medicines out of the four he is prescribed for that time, thus an electronic pill box could not capture the data of a complicated regimen. Running biochemical tests for each of these medications would be costly and impractical in a resource- constrained environment and would require repeat hospital visits [39–42]. In any arm, if the design required patients to make repeat visits during intervention and to interact with the caregiver then the act of repeated interaction may then be more responsible for adherence than the IT-based intervention itself. However, we do intend to perform a limited pill count to add robustness and triangulation data to our measures. Another limitation of our study is that we are unable to blind participants to the educational intervention, so those on the intervention arm are receiving SMS and are thus aware that they are on a program to increase literacy and medication compliance. A possible design to account for participant effect due to the lack of blinding could be giving two versions within the intervention where general information may be imparted in one arm and more detailed specific intervention could be imparted to participants in the second intervention arm as compared to the control. At this pilot stage we were unable to plan for two versions in this intervention arm since we were concerned about how this technology would be received and used in this early study.

Another limitation to the study is the application of the literacy tool TOFHLA in a developing country like Pakistan where the literacy rate varies between 28 and 96 %, varying sharply with age groups and regions. Since Karachi is the largest metropolitan city of the country with population of 9.3 million, literacy rate variations in this city are expected. In addition, the health system in Pakistan is very different to the US where this tool was designed. Hence, TOFHLA was modified and adapted to embrace the limitations encountered in our local community while we adhered to the basic architecture of TOFHLA. First, section 1 was modified to encompass our health system replacing insurance coverage with topics more pertinent to our local health structure. Second, passages in section 2 were completely over-hauled and replaced by our local data and advice by regional content experts. In addition, each statement was kept short and focused with just one blank to decrease the confusion that was anticipated with the presence of three to four blanks in the original version. The total numbers of questions in each section were kept the same to ensure accurate scoring as delineated in the original tool. This modified TOFHLA was content-validated by five experts each, from the fields of neurology, cardiology and epidemiology/statistics. After extensive fine-tuning, this tool was translated in Urdu and thereby successfully tested in the pilot. Our Cumulative Validity Index (CVI) scores for the regionally adapted TOFHLA were as follows: for relevance 0.87 and for clarity 0.72, which are excellent.

This study is regionally important. Pakistan, like other emerging low- and middle-income countries, faces non-communicable diseases like stroke and MI as its major health challenge, so a low-cost intervention would have a high impact [1, 4]. The study population is uniquely at high risk and exceptionally vulnerable to these two vascular diseases. Currently, the country has an electronic database with a unique identifier number, thus the potential of reaching masses as an extension is possible in addition to the already vast mobile infrastructure [43]. Since most out-of-pocket, large, unanticipated expenditure on vascular disease would push most Pakistanis into poverty, simple small steps in prevention would help and, even if the expected effect size is modest, we may ultimately have the potential to empower and positively influence many more lives [44–46].

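### Equal question counts are given as the ground for keeping the original TOFHLA scoring in a rewritten test, so the 0–59/60–74/75–100 literacy bands rest on an unsupported threshold

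*Protocol article*

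**What the plan says.** The Discussion describes three changes to the instrument:

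- Section 1: "section 1 was modified to encompass our health system replacing insurance coverage with topics more pertinent to our local health structure".
- Section 2 content: "passages in section 2 were completely over-hauled and replaced by our local data and advice by regional content experts".
- Section 2 format: "each statement was kept short and focused with just one blank to decrease the confusion that was anticipated" with the three to four blanks of the source version.

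It then gives the reason for keeping the scoring: "The total numbers of questions in each section were kept the same to ensure accurate scoring as delineated in the original tool".

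The Outcomes section sets out that scoring. For section 1, "this score out of 17 is converted to a weighted score, using a reference table, to a denominator of 50". For the rest, "Section 2 has a total of 50 questions, where each correct answer earns a score of 1". The total out of 100 is then banded, with a citation to a published source: "between 0 and 59 (inadequate), between 60 and 74 (marginal), and from 75 up to 100 (adequate".

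Statistical methods analyses the secondary outcome, change in TOFHLA, as a difference of proportions between arms by Pearson's chi-square or Fisher's exact test. It does not name the category to be counted. The only TOFHLA categories defined in the article are the three bands in Outcomes.

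The evidence offered for the modified tool is translation and back-translation, expert review ("This modified TOFHLA was content-validated by five experts each, from the fields of neurology, cardiology and epidemiology/statistics") with validity indices of 0.87 for relevance and 0.72 for clarity, and use in the pilot.

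**The concern.** A cut-off on a test score has meaning only through the difficulty of the items behind it. Whether a patient with a given level of literacy scores 58 or 76 depends on how hard the questions are, not on how many there are. Here content changed in both sections and format changed in section 2, yet the stated assurance of accurate scoring is the unchanged number of questions.

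Three things depend on the threshold:

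- what the adequate, marginal and inadequate labels mean in these patients;
- whether the band percentages can be set beside TOFHLA results from elsewhere;
- how large the between-arm difference in proportions is, and how easily it is detected, since both depend on where the cut falls in the score distribution.

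**Working it through.** **1. What equal counts secure.** Section 1 has 17 items converted to 50, section 2 has 50 items scored to 50, and 50 + 50 = 100. Keeping 17 and 50 items preserves these denominators and the 0–100 range. It fixes nothing about the expected score at a given level of literacy.

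**2. Whether other evidence fills the gap.** The relevance and clarity indices are expert ratings of content and wording. Back-translation concerns language. Pilot testing, in 20 patients, describes checking the data collection tool for question flow and comprehensiveness. No item difficulty, equating, criterion comparison or fresh derivation of the cut-offs is described. The Discussion names the use of TOFHLA in Pakistan as a limitation but offers the modification as the remedy; it does not mention the cut-offs.

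**3. Illustration of size.** The article gives no score distribution and no sample size or power for TOFHLA, so there is no planned figure to reproduce. The mean, SD, shift and gain below are all assumptions.

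Model: score ~ Normal(μ + d, σ), where d is the shift caused by the rewrite at unchanged literacy.

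- Adequate share = 1 − Φ((75 − μ − d)/σ).
- Inadequate share = Φ((60 − μ − d)/σ).
- Contrast = adequate share with a further 5 points in one arm, minus adequate share without.

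With μ = 60 and σ = 20, at d = 0 the adequate share is 1 − Φ(0.75) = 22.7%. With the gain it is 1 − Φ(0.50) = 30.9%, a contrast of 8.2 points.

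| Shift d | Adequate | Inadequate | Contrast for a 5-point gain |
|---|---|---|---|
| −10 (harder) | 10.6% | 69.1% | 5.3 points |
| −5 | 15.9% | 59.9% | 6.8 points |
| 0 | 22.7% | 50.0% | 8.2 points |
| +5 (easier) | 30.9% | 40.1% | 9.3 points |
| +10 | 40.1% | 30.9% | 9.9 points |

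**4. Other assumed distributions** (cuts at 59.5 and 74.5, to allow for whole-number scores):

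| Mean, SD | Adequate at d = 0 | Adequate at d = −10 to +10 |
|---|---|---|
| 55, 15 | 9.7% | 2.5% to 26.3% |
| 55, 20 | 16.5% | 7.0% to 31.7% |
| 65, 15 | 26.3% | 9.7% to 51.3% |
| 65, 20 | 31.7% | 16.5% to 51.0% |

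Across these scenarios the contrast for the same 5-point gain runs from 2.7 to 13.1 percentage points.

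**5. Sensitivity, banded against continuous.** Take 86 analysed per arm (the number before attrition in Sample size), two-sided 5%.

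- Proportions, μ = 60, σ = 20, d = 0: p₁ = 0.227, p₂ = 0.309. Under the null, SE₀ = √(0.268 × 0.732 × 2/86) = 0.0675. Under the alternative, SE₁ = √((0.227 × 0.773 + 0.309 × 0.691)/86) = 0.0672. Power = Φ((0.082 − 1.96 × 0.0675)/0.0672) = 23%. Over d from −10 to +10 it runs from 18% to 25%.
- Mean score, same σ: SE = 20 × √(2/86) = 3.05. Power = Φ(5/3.05 − 1.96) = Φ(−0.32) = 37%. A uniform shift d does not alter this figure.

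The second calculation uses the 3-month score alone. With baseline correlation r, adjustment multiplies the variance by 1 − r². Change from baseline multiplies it by 2(1 − r), which helps only if r exceeds 0.5.

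**The case against.** The strongest reply is that the trial asks about a difference between randomised arms, and both arms take the same instrument on the same schedule. An uncalibrated cut cannot create a difference where there is none. This stands in full. A reader might infer that the literacy comparison is biased; the documents do not support that. In the table above the contrast moves much less than the shares do.

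A reader might also infer that the rewrite made the test easier and so overstates adequate literacy. Single blanks point that way, but the section 1 topics and all section 2 passages were replaced too, and nothing reported fixes the net direction.

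The sentence on question counts can be read narrowly, as a remark about denominators. On that reading equal counts do serve their purpose. But the sentence claims accuracy of scoring as in the source tool, and Outcomes takes that scoring through to the bands. It remains true that the article does not say in so many words that equal counts justify the bands, and that Outcomes mentions a reference table for section 1 without saying it is the original one. Both are fair inferences rather than stated facts.

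Finally, the article condenses a fuller protocol, and further psychometric work may exist. That would not rescue the printed reason, which cannot support the cut-offs by itself. Nor does the article commit to a headline about adequate literacy: the abstract predicts only an improvement.

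**Conclusion.** The concern holds, within limits. Unchanged question counts preserve the score range and nothing more, and no reported evidence places the band boundaries at the same literacy level in the modified test. The direction of any shift is unknown.

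The between-arm comparison remains valid. The labels, comparison with other TOFHLA results, and the size and sensitivity of the difference in proportions rest on an unsupported threshold. Under the assumed mean of 60 and SD of 20, shifts of up to 10 points either way take the adequate share anywhere from 11% to 40%, but the contrast for a 5-point gain only from 5.3 to 9.9 points. These figures show scale; they are not estimates for this trial.

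This is a secondary outcome, and the change is a worthwhile, inexpensive improvement rather than a condition for the trial's validity.

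**What to change.** - **Statistical methods:** make the secondary literacy analysis a between-arm comparison of the 3-month modified-TOFHLA total score (0–100), adjusted for the baseline score or expressed as change from baseline, with a 95% confidence interval.
- **Outcomes:** keep the three bands as description only, labelled as not calibrated for the modified version.
- **Discussion:** replace the claim about equal counts. Say that they preserve the score range and that the cut-offs have not been validated for this version.

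Do not substitute a cut taken from the trial's pooled baseline distribution. It would be no better calibrated to literacy than the present bands.

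No new data are needed, since the score is already collected at both visits. The cost is more than wording: the trial is ongoing, and Ethics and human subjects' protection requires ethics committee approval and a registry report for any protocol change. The trial also gives up a familiar category headline.
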